### Data management

The data are stored in an electronic case report form (eCRF), using REDCap. Metadata are stored in the eCRF as well. Study monitoring is performed by in-house study monitors from the UMCG. Depending on the type of data and associated privacy regulations, data from the YOD-RiSoCo study will be made publicly available or will become available via the corresponding author, upon reasonable request.

### Statistical analysis

The analyses will be conducted in Statistical Package for the Social Sciences (SPSS). Assumptions for the intended analyses will be checked. Parametric tests will be used for normally distributed data, otherwise a non-parametric alternative will be used. For all analyses, the alpha will be set at 0.05, and analyses will be two-sided. In case of multiple comparisons, Bonferroni-Holm correction, or another appropriate correction, will be applied. Demographic variables will be analysed on a descriptive level (mean, standard deviation, frequency, percentage). To ensure matched groups of patients and controls, comparisons will be made on demographic variables with t-test (or non-parametric tests such as chi-square or Mann-Whitney U tests). Potential confounders will be included as covariates.

#### Study 1 New SC instruments.

Independent samples t-tests (or a non-parametric alternative, such as chi-square or Mann-Whitney U tests) will be performed to assess if the newly developed tasks can differentiate patients with bvYOD from healthy controls, based on social cognition, on a group level.

Construct validity of the newly developed measures will be assessed with parametric (such as Pearson’s correlation), or if more appropriate, non-parametric (such as Spearman’s) correlation analyses between the newly developed SC instruments, and existing SC instruments and other cognitive tests, respectively. It is expected that the new SC tests are significantly correlated to existing SC tests, indicating that the tests fall within the SC domain (convergent validity). However, no high correlation is expected, as the new tests measure different aspects of SC. No significant correlations are expected between the new SC tests and other cognitive measures (such as memory and attention), indicating that the tests measure SC specifically and no other cognitive domains, such as memory and attention (divergent validity).

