In patients with bvYOD, impairments can occur in all these aspects of SC, and especially emotional blunting and a lack of empathy are often reported by close others [10]. This lack of emotion experience and empathy might be related to problematic behaviour, such as risk-taking behaviour, as patients do not experience the signalling function of emotions, such as fear, to warn them for possible risks [11,12]. Furthermore they might also be unable to sufficiently experience the emotional impact of their actions on other people [11,12]. There is already some evidence of a relationship between SC aspects, including empathy, and problematic social behaviour, such as risk-taking behaviour [13–15]. However, studies into the relationship between empathy and risk-taking behaviour assess empathy with subjective questionnaires, or indirect measures, such as (functional) imaging data, for empathy, instead of performance-based measures.

Despite the importance of SC in the diagnosis of YOD and the impact of SC impairments on social behaviour, such as risk-taking behaviour, there is a lack of sensitive and valid neuropsychological tests for measuring SC aspects. To date, only tests for emotion recognition, and some ToM tests are validated and widely used. No valid performance-based instruments exist to measure the ability to experience emotions and to feel with another (empathy).

In conclusion, we state that 1) people with bvYOD often present with problems in social cognition and social behaviour, 2) impairments in different aspects of social cognition (emotion recognition, ToM, emotion experience and empathy) are related to problematic social behaviour, such as risk-taking behaviour, and 3) to date there is a lack of valid and reliable performance-based measures for these aspects of social cognition, in particular empathy and emotion experience, that are also predictive of such negative social behaviours. Therefore, the main aims of the YOD-RiSoCo study are the following:

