### Sample size

The aim of the YOD-RiSoCo study is to aid in the diagnosis of YOD by improving measurement of social cognition. Therefore, the main outcome measure is the difference between bvYOD patients and healthy controls in performance on the new SC instruments. This way we hope to differentiate pathology in bvYOD from healthy controls and to prove the sensitivity of the instruments for the specific pathology.

The estimated effect size is based on a previous study assessing the sensitivity of a new social cognition task [27]. In this study, significant differences were found between patients and controls in performance on the SNQ-NL Total score, with a large effect size (η_p_^2^ = 0.23). However, considering that no studies have yet been conducted with the current measurements and in the current population, a moderate effect size of 0.5 (default option) for the power calculation was chosen.

The power calculation was performed with *G*Power 3.1* [28]. For achieving 80% power, with 20% chance for making a Type II error and a 5% significance, the estimated sample size per group is 64. If the required number of approximately 128 inclusions is still not achieved within 24 months, the inclusion period will be extended with 6 months. In case of missing data, we will include additional subjects to reach the target N.

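### Study 1 reads non-significant correlations with other cognitive tests as specificity, and explains non-high correlations with social cognition tests as distinctness, without allowing for sampling or measurement error

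*Protocol article*

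**What the plan says.** The protocol article, under Statistical analysis, Study 1 New SC instruments, assesses construct validity by correlating the new SC instruments with existing SC instruments and with other cognitive tests. It states three expectations.

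- Convergent: "It is expected that the new SC tests are significantly correlated to existing SC tests, indicating that the tests fall within the SC domain".
- Size of the convergent correlation: "However, no high correlation is expected, as the new tests measure different aspects of SC". No value is given for what counts as high.
- Divergent: "No significant correlations are expected between the new SC tests and other cognitive measures (such as memory and attention"). The same sentence goes on to say that such a result indicates that the tests measure SC and not other domains.

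The general rule for testing is "For all analyses, the alpha will be set at 0.05, and analyses will be two-sided", with a Holm-type correction where there are multiple comparisons. The Background gives as part of the rationale that "there is a lack of valid and reliable performance-based measures for these aspects of social cognition". The stated aims are sensitivity, construct validity and, in Study 2, ecological validity.

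**The concern.** Two of the three expectations become easier to meet as a new test becomes noisier. Measurement error pulls every observed correlation towards zero, so it favours both a non-high correlation with SC tests and a non-significant one with other cognition. Sampling error adds to the second: a non-significant result in 64 or 128 people does not show that a correlation is absent or small.

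The new scales are short: 12 one-point items per ETIF subscale, six items per part of the Groningen Theory of Mind (ToM) battery, and three items for each of the cognitive and affective facets of its Story-based Empathy Task part. Low reliability is therefore plausible, although the article gives no figure.

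The construct-validity aim is at stake. A test that shares real variance with memory or attention could be reported as specific to SC. A low correlation with an established SC test could be put down to a new aspect of SC when part of the shortfall is error. Because the tests are meant to support diagnosis, users need to be able to tell these apart.

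**Working it through.** **1. The plan's own figure.** The Sample size section uses "a moderate effect size of 0.5 (default option) for the power calculation was chosen", with "For achieving 80% power, with 20% chance for making a Type II error and a 5% significance", and concludes that "the estimated sample size per group is 64". The two-sample t-test calculation (noncentral t, two-sided 5%) gives 63.77, so 64 per group, with power 80.1% at 64. The figure reproduces and is not in dispute. It is set for the group difference, not for the correlations.

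**2. Inputs.**
- From the article: two-sided alpha 0.05; n = 64 per group, 128 in total. The article does not say whether the Study 1 correlations are pooled or within group, so both sizes are shown.
- Assumed, because the article gives none: reliability of the new subscale 0.5 or 0.8; reliability of the comparator 0.8; true correlation 0.30 with a memory or attention test and 0.9 with an existing SC test.

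**3. Attenuation.** Observed r = true r × √(reliability of new test × reliability of comparator).
- Reliabilities 0.5 and 0.8: √0.40 = 0.632. So 0.30 × 0.632 = 0.19 and 0.9 × 0.632 = 0.57.
- Reliabilities 0.8 and 0.8: √0.64 = 0.80. So 0.30 × 0.80 = 0.24 and 0.9 × 0.80 = 0.72.

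**4. Chance of a non-significant result for the true r of 0.30.** Power ≈ Φ(z·√(n − 3) − 1.96), where z = atanh(observed r); the opposite tail is negligible. √61 = 7.81 and √125 = 11.18.

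| Reliabilities | Observed r | z | Non-significant, n = 64 | Non-significant, n = 128 |
|---|---|---|---|---|
| 0.5 / 0.8 | 0.19 | 0.192 | 1 − Φ(−0.46) = 68% | 1 − Φ(0.19) = 42 to 43% |
| 0.8 / 0.8 | 0.24 | 0.245 | 1 − Φ(−0.05) = 52% | 1 − Φ(0.78) = 22% |
| 1 / 1 | 0.30 | 0.310 | 1 − Φ(0.46) = 32% | 1 − Φ(1.50) = 7% |

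The range 42 to 43% reflects rounding: r = 0.190 gives 42.4% and the unrounded 0.1897 gives 42.6%. The last row shows sampling error alone. A multiplicity correction, if applied to these correlations, would raise every figure.

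**5. What a non-significant result leaves open.** The critical |r| is 0.246 at n = 64 and 0.174 at n = 128. An observed r of 0.24 at n = 64 has 95% CI tanh(0.245 ± 1.96/7.81), from −0.01 to 0.46. An observed r of 0.17 at n = 128 has 95% CI tanh(0.172 ± 1.96/11.18), from −0.00 to 0.33. Both are non-significant, and both are compatible with correlations that few would call negligible.

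**6. The limit of the argument.** The same factor shrinks the SC correlation. At reliabilities 0.5 and 0.8, the true SC correlation must be about 0.174/0.632 = 0.28 at n = 128, or 0.246/0.632 = 0.39 at n = 64, for the observed value to sit at the critical value. With a true r of 0.30 in both domains, neither correlation would be reliably significant. The misleading combination arises when the true SC correlation clearly exceeds the true correlation with other cognition. For example, a true SC r of 0.9 observed as 0.57 is significant in more than 99% of samples even at n = 64.

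**The case against.** **A reader might infer that the plan treats a middling correlation as proof of a distinct construct.** It does not. The text speaks of expectations and indications. In the sentence on non-high correlations, distinctness is the reason for the prediction, not a conclusion drawn from the result. The firmer inferential step is the divergent one, where non-significance is taken to indicate specificity.

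**A reader might also infer that any unreliable test would pass.** It would not. The plan expects a significant correlation with existing SC tests, and its main outcome is a difference between patients and controls. Noise works against both. Where the pattern does arise, the conclusion that the test belongs broadly to the SC domain is probably right; the claim that it measures nothing else is the one in doubt.

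**The missing reliability analysis is not in itself an error.** This is a condensed article, and a full protocol or analysis plan, not shown, may contain one. That objection stands. It does not repair the stated way of reading non-significance.

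**Part of the weakness has nothing to do with reliability.** With perfect measurement, a true r of 0.30 is still missed 32% of the time at n = 64. This is correct, and it is why a change to the divergent rule matters more than reliability estimates.

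**Correcting for attenuation is not always possible.** It needs the comparator's reliability, and timed or count scores such as the Trail Making Test, the Symbol Digit Modalities Test and fluency do not suit alpha. Some comparator results may be imported from earlier assessments. Storage of item scores is implied by the scoring and not stated, no scoring is described for the NEET, and some ETIF and Faux Pas questions depend on an earlier answer. These limits stand, so the correction can only be a sensitivity analysis.

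**A high correlation between ETIF identification and FEEST need not be required.** Both concern recognising another person's emotion, but one uses spoken video narratives and the other facial expressions. A non-high value is a defensible prediction.

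**Conclusion.** The point holds in a limited form. The stated divergent rule can label a test as specific to SC when it has a real correlation with other cognition, and the advance explanation of non-high SC correlations leaves no room for error of measurement. For a true r of 0.30, the chance of a non-significant result is about 68% (n = 64) and 42 to 43% (n = 128) at reliabilities 0.5 and 0.8, and about 52% and 22% at 0.8 and 0.8. A near-redundant pair with true r 0.9 shows 0.57 and 0.72 in the same two cases.

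All reliabilities and true correlations here are assumptions. The result applies where the true SC correlation is clearly the larger of the two. The sample size and the comparison of patients with controls are not affected. This is an inexpensive improvement to how construct validity is judged, not a flaw in the design.

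**What to change.** 1. Do not infer specificity from non-significance. Report each validity correlation with a 95% CI. Judge divergence by the size of the correlation against a bound stated in advance, or by comparing the convergent with the divergent correlation in the same participants.
2. Where item scores exist (ETIF, Groningen ToM battery), report internal consistency with a CI for each new subscale, separately in patients and controls. Choose a coefficient that respects the conditional questions.
3. Where the comparator's reliability is also available, give attenuation-corrected correlations as a sensitivity analysis. Do not read a low correlation as a distinct construct when the subscale is shown to be unreliable.
4. A fixed reliability floor such as 0.6, and a separate expectation for ETIF identification with FEEST, are optional.

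Cost: a few lines of plan text and a little extra analysis, with no new testing. Corrected correlations have wider intervals, some specificity claims will be left open, and some subscales may prove too unreliable to interpret.

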## Methods and materials

### Study design study 1

Study 1 of the YOD-RiSoCo study is an observational prospective cohort study, that aims to include 64 patients with bvYOD and 64 healthy controls. Controls will be matched to patients on a group level, so that sex, age, and educational level distributions do not significantly differ between groups. The recruitment of controls will be adapted to match the included patients.

### Study design study 2

Study 2 of the YOD-RiSoCo study is an observational study that aims to include 20 patients with bvYOD, 20 healthy controls, 20 non-bvYOD patients and 20 patients with brain injury affecting frontal processes. The bvYOD and healthy control patients will be included from Study 1 (Fig 1).

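### Study 1 reads the absence of a significant correlation as divergent validity, and does not say how group is handled in the construct-validity correlations

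*Protocol article*

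**What the plan says.** The protocol article, Statistical analysis, Study 1 New SC instruments, plans Pearson or Spearman correlations of the new SC tests with existing SC tests and with other cognitive tests. A significant correlation with existing SC tests is taken to show convergent validity, with the remark "However, no high correlation is expected, as the new tests measure different aspects of SC". For divergent validity: "No significant correlations are expected between the new SC tests and other cognitive measures (such as memory and attention), indicating that the tests" capture SC and not domains such as memory or attention. No cut-off for a high correlation, no bound on a divergent correlation and no confidence interval is given.

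The general part of Statistical analysis states that "the alpha will be set at 0.05, and analyses will be two-sided", and "In case of multiple comparisons, Bonferroni-Holm correction, or another appropriate correction, will be applied". It adds a general sentence that potential confounders will enter as covariates.

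Study 1 "aims to include 64 patients with bvYOD and 64 healthy controls". Its section does not say whether the correlations are run over both groups, within each group, or adjusted for group. The corresponding section for Study 2 does say that its correlations are run in the separate groups.

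**The concern.** Construct validity is the second of the three stated aims, and the divergent half of it rests on not rejecting a null hypothesis. Non-significance reflects the size of the correlation, the sample size and the significance threshold together. A new test that shares real variance with memory or attention can therefore be called SC-specific because the study was imprecise. A Holm correction normally makes a claim harder to support. Here success is non-significance, so it makes the claim easier.

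The second issue is the handling of group. Two tests that are unrelated within patients and unrelated within controls will still correlate in the combined sample if patients score lower on both. That could lend false support to convergent validity, or make a specific test look non-specific. Running the correlations within group removes this problem but leaves 64 participants, where the non-significance rule is at its weakest.

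**Working it through.** **The plan's own figure.** In Sample size, "a moderate effect size of 0.5 (default option) for the power calculation was chosen"; "For achieving 80% power, with 20% chance for making a Type II error and a 5% significance", "the estimated sample size per group is 64". The two-sample t calculation with d = 0.5, two-sided 0.05 and power 0.80 gives 63.8, so 64 per group, with power 0.801. The figure is reproduced. It concerns the group difference only; no calculation is given for the correlations.

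**Step 1: what counts as significant.** Critical r = t/√(n − 2 + t²).
- n = 128: t = 1.979, so 1.979/√(126 + 3.916) = 0.174.
- n = 64: t = 1.999, so 1.999/√(62 + 3.996) = 0.246.

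An observed r of 0.173 with 128 participants is just non-significant and would pass as divergent, although its 95% confidence interval runs from about 0.00 to 0.34.

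**Step 2: how often a real correlation is missed.** Power ≈ Φ(atanh(r)·√(n − 3) − z).
- True r = 0.20, n = 128: 0.2027 × 11.180 − 1.960 = 0.307; power 0.62; missed 38%.
- True r = 0.30, n = 64: 0.3095 × 7.810 − 1.960 = 0.457; power 0.68; missed 32%.

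**Step 3: effect of the correction.** The article does not define the family. Table 1 lists nine general cognitive measures; with three new instruments, 9 × 3 = 27 tests (assumption). The first and strictest Holm step is 0.05/27 = 0.00185, z = 3.113.
- True r = 0.30, n = 64: 2.417 − 3.113 = −0.696; power 0.24; missed 76%.
- With seven performance tests only, 7 × 3 = 21 tests (also an assumption), power is 0.27; missed 73%.

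Later Holm steps are less strict, so these are upper figures.

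**Step 4: correlation produced by group alone, if pooled.** With equal groups and zero within-group correlation, r = (d₁d₂/4)/√[(1 + d₁²/4)(1 + d₂²/4)]. The cited partial η² of 0.23 for an existing SC test converts, for two equal groups, to d = 2√(0.23/0.77) = 1.09.

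| d on the two tests | Induced r | Significant at 0.05, N = 128 |
|---|---|---|
| 0.5 and 0.5 | 0.0625/1.0625 = 0.06 | about 10% |
| 1.09 and 0.5 | 0.1366/√(1.2987 × 1.0625) = 0.12 | about 26% |
| 1.09 and 1.09 | 0.2987/1.2987 = 0.23 | about 74% (Fisher z) to 77% (simulation) |

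The percentages come from 20,000 simulated studies of 64 + 64, with the Fisher approximation added in the last row. With group partialled out, false significance was close to 5% in every one of these scenarios.

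**Step 5: what a bound would deliver.** Assume a bound of |r| < 0.30 and a true r of 0. The chance that the 95% interval lies inside the bound is 2Φ(atanh(0.30)·√(n − 3) − 1.96) − 1.
- n = 128: 2Φ(1.50) − 1 = 87%.
- n = 64: 2Φ(0.457) − 1 = 35%.

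**The case against.** The divergent sentence is worded as an expectation, not as a formal pass/fail rule, and the correlations will be available to readers whatever label is attached. That softens the point but does not remove it: the same sentence says what a non-significant result would indicate, and offers no other criterion.

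On group, the article is silent, and a condensed article may leave this to the full protocol. The covariate sentence could cover it, and demographic and diagnostic data are collected partly to account for confounding. Neither passage names group, however, and a plain Pearson or Spearman correlation takes no covariate. What stands is that the article does not settle the matter for Study 1 although it does for Study 2.

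A reader might infer more: that convergent validity must pass and divergent validity must fail. The documents do not support this. Pooling is not stated, and no patient-control difference on general cognition is given. The Abstract and Background describe behavioural variants as presenting with social change and not with memory loss, so a large memory deficit cannot be taken for granted. At the planning value of 0.5 on both tests the induced correlation is small.

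Nor does it follow that the second aim cannot be answered, since the data will support a sound analysis. The absence of a planned reliability estimate is also no finding, because an article may leave it out.

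**Conclusion.** The inference from non-significance to divergent validity is wrong as written, and this does not depend on how group is handled. At 0.05 it lets through a true correlation of 0.20 in 38% of cases with 128 participants, and one of 0.30 in 32% of cases with 64. The 76% figure rests on the assumed family of 27 and the first Holm step.

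The group issue is conditional on pooling. Its size runs from negligible to material over the range shown. The planning value of 0.5 and the cited effect of about 1.09 come from the article. Applying either to a given pair of tests, especially to a general cognitive test, is an assumption, because the 0.5 was chosen for the new SC tests and the 1.09 belongs to an existing SC test in another study.

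This should be fixed before analysis. The main outcome and the sample size are unaffected.

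**What to change.** - Remove the statement that non-significant correlations indicate divergent validity.
- State how group is handled in Study 1. Report correlations partialled for group, or within patients and within controls, each with a 95% confidence interval.
- Judge divergence in one of two ways: compare each new test's correlation with existing SC tests against its correlation with general cognitive tests (a test for dependent correlations, or a bootstrap interval for the difference), or require the interval for the divergent correlation to lie inside a bound on |r| fixed in advance.
- Do not let a multiplicity correction help any criterion whose success is non-significance.

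The cost is analysis wording only; the measures needed are already planned. The claim may be softer. With the assumed bound of 0.30, the 87% against 35% in Step 5 makes a group-partialled analysis of all 128 participants preferable to relying on 64 patients. That analysis assumes broadly similar within-group correlations, so the within-group estimates should be shown beside it.
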